#### 2.8.3. Usual Care (Control Group)

Control group participants will receive only the usual care. Standard care includes providing written information on diabetes and brochures for raising awareness, including the benefits of modifying their health behaviours. Generally, T2DM patients have regularly scheduled visits to check diabetes management by endocrine specialists. The visit’s main purpose is to check whether the patient’s medications need to be replaced, increased, or continue with the same prescription.

### 2.9. Measures

Different tools and measures will be used to assess the primary and secondary study’s outcomes as presented in below sections. To reduce the risk of bias, an independent interviewer will be trained and supervised by the researchers to undertake the role of collecting some data, including semi-structured interviews and providing questionnaires. The interview guide will be developed by the researchers and used by the interviewer to guide the interviews. The interviewer will remain blind to the intervention details, process, and activities. Control group participants will be requested to complete pre- and post-intervention measures and questionnaires.

#### 2.9.1. Primary Outcome Measures

##### Feasibility

The primary outcome will assess the feasibility, including recruitment rates of the study and retention, and acceptability of the intervention by participants. During this step, the researchers seek to measure the possibility of recruiting sufficient participants within a specific period and the number of recruited participants who completed the study. Participants’ responses and expressions of their engagement interests will be recorded, including reasons for interest, reasons for engagement, and reasons for not interest. The number and percentage of interested eligible, complete, and drop-out participants will be recorded to explain the recruitment rates and retention. In addition, the researchers will undertake a qualitative process evaluation to investigate participants’ and their physicians’ experiences and feedback on the intervention, including assessment of the most appropriate advertising method for the intervention. Different questionnaires will be used to provide further information. In addition, the health coach also will report on his experience with participants.

##### Acceptability

Qualitative and quantitative data will be used to assess to what extent the intervention and its implementation are acceptable to the patients. The purpose of assessing the implementation process is to identify any potential problem with the methodology used to deliver the intervention. The acceptability of the implementation process, including data collection procedures, will be assessed by conducting post-intervention semi-structured qualitative interviews, informal meetings and focus groups. Interview guidance will be used to direct the conversations and enable the researchers to explore more details about how the participants find and describe their intervention experience. A questionnaire will be used to quantify the participants’ self-reported satisfaction (Likert-scale Satisfaction Questionnaire, 14-items). Healthcare providers and participants’ opinions are important to help adapt the intervention in terms of ensuring that it corresponds with and is acceptable for the Saudi cultural context.

#### 2.9.2. Secondary Outcome Measures

The secondary outcomes (preliminary efficacy) comprise anthropometric, clinical, and psychological variables selected as of the standard measures for monitoring and prevention of complications in diabetes [44]. These variables will be assessed twice at the intervention, at baseline and after 3 months for HbA1C, blood pressure, body mass index (BMI), weight and waist circumference. Change in outcomes post-intervention will help to determine if the intervention is feasible, acceptable, and effective. Table 3 provides the timeline for the assessment of the variables.

#### 2.9.3. Demographic Information

Demographic information will be used to explain the nature of the recruited participants in the intervention. It will be collected at a single time during the intervention baseline.

#### 2.9.4. Fidelity Assessment

Qualitative data, including interviews, focus groups, meetings, and coaching sessions will be audio recorded, transcribed, and translated into English. Thematic analysis will be used to analyse qualitative data. Multiple audio recorders will be used to ensure high reliability, and they will be transcript to text by two independent native Arabic speakers. Final coding will be used after reaching an agreement between the independent transcribers. Translation to English will be the next step completed by the researchers and an additional check of meaning by an independent native Saudi Arabian Arabic speaker.

#### 2.9.5. Predetermined Progression Criteria to Proceed to a Larger Trial

Before the feasibility of RCT started, the research team developed progression criteria. The progression criteria will help to decide on carrying out a full scale based on the findings generated from the feasibility study regarding recruitment, retention, adherence, and overall acceptability [45]. These criteria establish the benchmarks for assessing the trial’s feasibility and determining whether undertake a further larger-scale study. The predetermined progression criteria are presented in Table 4.

#### 2.9.6. Data Management

Both textual and audio data will be generated and collected using different research methods. The textual data are (i) clinical observations and field notes; (ii) notes collected from formal and informal meetings with healthcare staff; and (iii) field notes from the health coaching sessions. The audio data will consist of (i) recordings of some formal and informal meetings with healthcare professionals; (ii) recordings from health coaching sessions; and (iii) recordings from focus groups. All recordings will be immediately downloaded on separate devices.

The majority of raw quantitative data will be stored as tabular data copies in Microsoft Excel format to allow for statistical analysis via (SPSS). Thematic analysis will be used to analyse qualitative data. Multiple audio recorders will be used to ensure high reliability, and they will be transcript to text by independent native Saudi speakers. Qualitative data will be stored temporarily on multiple hard drives, e.g., USB and Google Drive, and manual copies, e.g., handbooks and logbooks. Separate files will be used for each type of qualitative data for organising purposes. For ensuring the long-term usability of data, they will be stored in a secure place within (KFMC governmental institution) for confidentiality purposes and participants’ privacy. Additional space storage will be requested from the University of Sheffield to ensure that enough multiple copies of data are there in case of any potential risk, for example, losing some data due to storage abilities or difficulty in accessing any other technical issues. I will continuously make backups of the files on external hard devices and in a safe and secure place through (KFMC and the University of Sheffield).

Qualitative data, including interviews, focus groups, meetings, and coaching sessions will be recorded on electronic recorders, transcribed, and translated. There will be interview guidance used to direct the conversations and enable the researchers to obtain the intervention’s information. All participants will be given a unique reference number used when referring directly to their responses. Quantitative data will be generated and collected by the researchers with support from the centre’s health professionals, including HbA1c, BMI, blood pressure, weight and waist circumference. All data will be encrypted using a high-level encryption method to protect collected data (using FileVault on Mac) and the University Data Centre.

The researchers will be monitoring the quality of data from the beginning until the intervention endpoint. Data will be organised based on its type (e.g., interviews, coaching sessions, etc.), in separate files within one folder for easy access to each type at any time. Multiple copies of the folder will be backed up and stored throughout the period of data collection. Backups with up-to-date data will be completed continuously to keep data safe and updated. Qualitative data will be recorded to avoid accidentally missing information. This would allow for assessing the consistency and quality of the data collected. Vitro measures will be taken by a health practitioner (e.g., laboratory specialist) from KFMC in Riyadh. Multiple samples will be taken to ensure the quality of results by comparison.

## 3. Data Analysis

### 3.1. Quantitative Data

The feasibility and acceptability of the study’s findings will be evaluated in relation to the quantitative data using descriptive analysis. The descriptive analysis covers different aspects as the following:Screening, recruitment process, retention and adherence (coaching sessions) rates will be calculated and presented as proportionsLength of time to recruit the target sampleDuration of time needed to complete the assessmentsPercentage of completed interventions sessionsAverage time needed to complete each sessionDescription of participants interaction during coaching sessions (frequent BCTs used, interactions with coaches)Acceptability and suitability of intervention through participants’ perceptions of, and experiences with, the health coaching intervention (Satisfaction Questionnaire)Additionally, other outcome measures such as diabetes self-management and patient self-efficacy will be evaluated at baseline and endpoint to investigate changes in participants’ behaviours compared to another groupPreliminary effects of the interventionRegarding the evaluation of the preliminary efficacy of the intervention, secondary variables will be described by means and S.Ds, investigated pre- and post-intervention to measure changes in the outcomes; glycosylated haemoglobin (HbA1C), blood pressure, body mass index (BMI), waist circumference, weight, patients’ self-efficacy, and diabetes self-managementCorrelations will be performed between:The number of completed coaching sessions and A1c, BP, BMI, WC body weight at 3 monthsThe number of completed coaching sessions and self-efficacy and diabetes self-management scales at 3 months

### 3.2. Qualitative Data

Qualitative data, including interviews, focus groups, meetings, and coaching sessions will be audio recorded then transcribed, and translated into English. Thematic analysis will be used to analyse qualitative data. Multiple audio recorders will be used to ensure high reliability, and they will be transcript to text by independent native Saudi Arabian speakers. The qualitative analysis includes the following:

All interviews and focus groups are recorded and transcribed

A total of 10% of transcription will be translated from Arabic to English, back-translated for accuracy and validity purposes, and checked by a professional native speaker.

To prevent meaning from being lost in translation, to improve the validity of the data, which might be compromised if it is translated, and to expedite the process, the analysis will be carried out in the original language [46].

The analysis will be conducted by using:
oA reflexive thematic analysis [47];oFrom a Pragmatic philosophical standpoint [48];oThematic analysis will be manually conducted using NVivo software.

Next, all interactions with the health coaches through the coaching sessions will be mapped to the BCW and the BCTTv1 using NVivo for coding used BCTs. The final step is integrating QUALI and QUANT data and analysing them as they occurred concurrently simultaneously per the thesis process diagram (convergent design).

## 4. Discussion

Changing lifestyle is widely recognised as the key to supporting people with T2DM to adopt healthy behaviours to control their condition. An individualised, self-management approach for non-communicable diseases such as T2DM is now urged to a more prominent degree than at any other time [49,50]. Several studies have reported the positive effects of lifestyle intervention programmes among people at high-risk, with a 58% decrease in the incidence of T2DM [51,52]. Utilising a lifestyle intervention aims at reducing the probable risks of chronic diseases in addition to decreasing the occurrence of such conditions, if already existent, as part of a management plan. Adopting a healthy diet accompanied by physical activity is likely to decrease the risk of T2DM by 45% regardless of genetic risk [11]. Different studies have found that chronic diseases such as T2DM can be effectively addressed using health coaching programmes, which aim to promote healthy behaviours [53]. Moreover, studies have demonstrated the effectiveness of health coaching with a variety of chronic illnesses, including T2DM [21]. 

Conducting the feasibility study will help inform the research development process by identifying key uncertainties in the study before a future full-scale intervention is carried out. It is hoped that the findings of the present study will contribute to informing the research field of health coaching on T2DM and to ensure the intervention achieves a good fit with a new context; namely, Saudi patients with T2DM. Since health coaching as a new approach is now included in the Saudi Ministry of Health’s (MOH) future plans, the study findings can directly inform future policy developments in SA. Additionally, it is hoped that the present study will make a significant contribution to the literature as it represents the first study that has been developed based on the use of specific “active ingredients” (BCTs), which directly match the intervention’s underpinning theories. Consequently, health coaching intervention designers may benefit from the study’s findings by allowing them to interpret and identify effective BCTs to facilitate future replication. Finally, the study’s findings could lead to the increased uptake of other behaviour change interventions in the Saudi Arabian context.

## Figures and Tables

**Figure 1 ijerph-19-15089-f001:**

Health coaching intervention sessions biweekly.

**Table 1 ijerph-19-15089-t001:** The BCTs selected and its link to the key barriers and intervention functions.

COM-B		TDF	Barrier	Intervention Function	BCTs
Capability	Psychological	Knowledge	Poor T2DM knowledge affect self-control Poor nutrition knowledge (what the association between diabetes and diet, type of healthy food) Poor knowledge about PA (how to engage in PA, how much time spend on PA, PA intensity, PA types, underestimate the role of PA	Education	5.1 Information about health consequences
	Physical	Physical skills	Lack of energy to do PA Lack or limited skills of physical skills to do exercise	Enablement Training	Enablement: 6.1 Demonstration of the behaviour 1.5 Review behaviour goal (s) 1.7 Review outcome goal (s) 2.3 Self-monitoring of behaviour 12.1 Restructuring the physical environment 4.1 Instruction on how to perform a behaviour’ 3.1 Social support (unspecified) Training: 8.1 Behavioural practice/rehearsal 8.3 Habit Formation 8.4 Habit reversal 8.7 Graded tasks 15.4 Self-talk 10.9 Self-reward 2.2 Feedback on behaviour 2.3 Self-monitoring of behaviour
Opportunity	Social	Social influences	Social norms and habits: overuse of high calories food intake; carbohydrates and fats, eating together (collectives), and social courtesy to eat unhealthy diet	Enablement	Enablement: 1.3 Goal setting (outcome) 1.1 Goal setting (behaviour) 3.1 Social support (unspecified) 1.4 Action planning 1.2 Problem-solving 2.3 Self-monitoring of behaviour 8.7 Graded tasks 5.5 Anticipated regret 12.1 Restructuring the physical environment 12.2 Restructuring the social environment
	Physical	Environmental context and resources	Lack of time Lack of resources (environmental, appropriate climate and financial ability) Lack of access to do activity Overuse of cars for transportations	Restriction Environmental restructuring Enablement Modelling	Enablement: 1.3 Goal setting (outcome) 1.1 Goal setting (Behaviour) 3.1 Social support (unspecified) 1.4 Action planning 1.2 Problem-solving 2.3 Self-monitoring of behaviour 9.2 Pros and cons 9.3 Comparative imagining of future outcomes 8.7 Graded tasks 1.9 Commitment 13.2 Framing/reframing 5.5 Anticipated regret 12.5 Adding objects to the environment Modelling: 6.1 Demonstration of the behaviour Environmental restructuring: 12.1 Restructuring the physical environment 7.1 Prompts/Cues Restriction: Use rules to reduce opportunity to engage in unwanted behaviour
Motivation	Reflective	Beliefs about own capability	Lack of willpower and self-confidence to do PA and maintain healthy diet	Persuasion Education Enablement	Persuasion: 15.1 Verbal persuasion about capability 15.2 Mental rehearsal of successful performance 9.1 Credible source 2.2 Feedback on behaviour 13.2 Framing/reframing 15.3 Focus on past success Education: 5.1 Information about health consequences 5.3 Information about social and environmental consequences Enablement: 1.9 Commitment 5.5 Anticipated regret
		Beliefsconsequences	Fear from consequences of PA (fear of injury and disease future complications)	Education	5.1 Information about health consequences
		Social role and identity	Struggle to change social identity associated with culture diet Struggle to accept the fact of living with diabetes	Education Persuasion	Education: 5.1 Information about health consequences Persuasion: 13.5 Identity associated with changed behaviour

**Table 2 ijerph-19-15089-t002:** Health coaching intervention detailed protocol.

Phase #	Session Content	Session Goals	Intervention Function
1	Session #1, the patient’s assessment form and consent supposed to be completed General introduction about the health coaching intervention Outline the intervention structure and content Discuss the coach’s roles and the expectations from the participant (being completely clear with the client about the health coaching) Creating an alliance (Establish Trust) Learn from a patient (disease history, obstacles, priorities, strengths, goals, etc.) Help patient to create wellness vision Assess the readiness of patient’s stage in relation to change health behaviour (the transtheoretical model) Introduce the importance of having a healthy diet Introduce the importance of increasing physical activity Increase awareness of adopting a healthy lifestyle in relation to controlling diabetes Identify 3-month general behavioural goals and biweekly goals Explore resources needed to help achieve desirable behaviour Commitment	Identifying the patient’s current position in the overall health status (via the transtheoretical model) Build up a relationship (as an ally) between patient and coach Encourage open discussion Make sure the patient understands what health coaching is Allow the patient to develop a foundational conception of goal setting and action planning The patient creates (SMART) measurable, action-based, realistic and timely achievable goals Have better control of carbohydrate and fat intake Gradually increase physical activity Gradually increase achievable tasks until the intended behaviour is achieved	Education Enablement Training Restriction Environmental restructuring
2	Phase #2 (session # 2), (this phase will be used again in sessions # 4 and 5) Check ongoing progress Understand patient’s state (use reflections) Ask patient to share views (so far) of good things that occurred and experiences from last session Use positive reflections about patient’s strengths, passion or emotions Ask patient to assess the previously selected short goals and accomplishments Use reflections to understand potential barriers prevent patient from achieving past goals Identify specific strategies that they may use to overcome the obstacles Explore what patient learned from past experience Ask and discuss with patient next short goals Share feedback on patient’s progression Ask patient to connect current accomplishments to the general 3-months goals Review the general goals to see if patient want to revise them (to be more realistic and achievable) Affirm the patient’s choices, strengths, and capability Use techniques such as reflective listening to address ambivalence and respond to the patient’s resistance (motivational interviewing)	Assessment of progression Review goal setting (behaviour) Review behaviour goals to examine a patient’s performance progression toward the agreed goals Enable patient to develop problem-solving skills Enable patient to create action plan Prompt the participant to generate ideas and strategies to overcome barriers (problem-solving) Allow patients to monitor their behaviours (know the changes so far) Keep patient motivated (no matter the accomplishments)	Persuasion Education Enablement Training Restriction Environmental restructuring
3	Middle phase (session # 3), the coach continues to observe the patient and give feedback to help them move forward in achieving their goals through bi-weekly SMART goal setting. Patient continues to identify strategies to address existing obstacles and enhance their self-ability If goals are not achieved, the barriers will be identified, action plan will be taken to address these obstacles and modified goals will be created The coach will assess the patient’s self-efficacy by scoring goals to measure the participant’s confidence in achieving their goals The coach continues using the skills needed to explore ambivalence and discrepancies between the participant’s plans and their actual behaviour (Rollnick et al., 2005) Affirmations and appreciative inquiry will be used to appreciate progression and improve patients’ self-confidence	Assessment of current behavioural change Review goal setting (behaviour) Review behaviour goals to examine a patient’s performance progression toward the agreed goals Review all previous goals and reassess goal progress Enable the participant to assess their progress Prompt the participant to analyse factors influencing their behaviour Participant’s commitment to affirm to review and change behaviour	Persuasion Education Enablement Training
4	(session # 6) Conclude the coaching relationship Determine where the patient is in terms of their goals How the coach can best guide the client, and whether coaching is what will best benefit the client Participants’ assessment of the intervention, general satisfaction of the participant with the process Appreciate the patient’s engagement in the intervention Explore the patients’ experience and how future coaching intervention would best support T2DM	Allow patient to explore the difference at the endpoint Learn for participants’ experience Findings from the feasibility study will be used to justify an expansion of the study (full-scale) or refined for better outcomes so that we can carry out a large RCT on the efficacy of this intervention	Persuasion Education

**Table 3 ijerph-19-15089-t003:** Timeline for the assessment of the intervention measurements.

Study Timeline				
Pre-Study Allocation			Post-Study Allocation	
Activity	Enrolment	Allocation	Baseline	Endpoint
Intervention advertising				
Screening eligibility				
Informed consent				
Baseline measures				
Randomisation				
Allocation				
Start of the Study:				
Intervention group				
Control group				
Assessments:				
Demographic				
BMI				
Weight				
Blood pressure				
Waist circumference				
HbA1c				
Feasibility Questionnaire				
Summary of Diabetes Self Care Activity (SDSCA), 12-items				
Self-efficacy Scale for Diabetes, 8-items				
Acceptibity Questionnaire				
Likert Scale Satisfaction Questionnaire, 14-items				

**Table 4 ijerph-19-15089-t004:** Health coaching predetermined criteria.

Criteria	Predetermined Cut-Offs
Screening prospective participants	If 60–80% or more of those eligible to participate in the study consented, this supports conducting a large RCT scale trial, but if percentage is less than 50%, there is no significance to move forward.
Recruitment rate	If the recruitment rate of people who were eligible and consented was ≥80% this would support conducting a large RCT trial. If the rate was between 70–65%, this needs further discussion to explore the reasons and whether, if they can be modified, then the trial may progress with cautions. If the rate was ≤65%, there is no significance to moving forward.
Retention rate at 3-months	If the rate was ≥83%, this supports conducting a large RCT scale trial If the rate was less than 83%, there is no significance to moving forward.
Intervention adherence	If the adherence rate was ≥84% of the intervention (≥5 out of the 6 coaching sessions) If the rate was between 84–67% (≥5.4 out of the 6 coaching sessions), this needs further discussion to explore the reasons and whether, if they can be modified, then the trial may progress with cautions. If the adherence rate was less than 67%, there is no significance to moving forward.

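### Table 4 does not work as a predetermined progression rule: two rows leave results without a verdict, the recruitment rate has no distinct denominator, and the promised acceptability criterion is absent

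*Protocol article*

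**What the plan says.** Section 2.9.5 of the protocol article states that progression criteria were fixed in advance. The decision on a full-scale trial is to be "based on the findings generated from the feasibility study regarding recruitment, retention, adherence, and overall acceptability", and the section refers the reader to Table 4 for the criteria.

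Table 4 has four rows: screening of prospective participants, recruitment rate, retention at 3 months, and intervention adherence. The first two concern this point.

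- **Screening row.** Go: "If 60–80% or more of those eligible to participate in the study consented, this supports conducting a large RCT scale trial". Stop: "but if percentage is less than 50%, there is no significance to move forward".
- **Recruitment row.** Go: "If the recruitment rate of people who were eligible and consented was ≥80% this would support conducting a large RCT trial". Caution: "If the rate was between 70–65%, this needs further discussion to explore the reasons". Stop: "If the rate was ≤65%, there is no significance to moving forward".

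Section 2.9.1 makes acceptability to participants part of the primary outcome and plans a 14-item Likert satisfaction questionnaire to quantify it. Section 2.7 plans 30 participants, 15 per group.

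**The concern.** Deciding whether to run a full trial is the purpose of this study, and Table 4 holds the benchmarks for that decision. A rule set in advance is useful only if each possible result leads to one verdict. Where a row is silent, or where two rows may be judging the same proportion by different cut-offs, the team would have to supply a verdict or pick a row after seeing the data. That removes the protection the rule was meant to give. The missing acceptability row is a separate gap: the text says the criteria cover that domain, and the table to which it refers has no benchmark for it.

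**Working it through.** There is no stated power or sample-size figure to reproduce. The check applies the two rows as worded to every possible percentage.

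**Inputs (Table 4).** Go means the row supports a large trial, caution means discuss and possibly proceed, and stop means do not move forward.

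- Screening row, consented ÷ eligible: go at 60% or more (the lower edge of the stated range), stop below 50%.
- Recruitment row, denominator not defined: go at 80% or more, caution from 65% to 70%, stop at 65% or below.

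**Step 1: each row alone, whatever its denominator.**

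- Screening: 50% to <60% is neither go nor stop, so there is no verdict.
- Recruitment: >70% to <80% is in no band, so there is no verdict. Exactly 65% meets both the caution and the stop condition.

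The recruitment gap does not depend on the denominator. Suppose the rate were the number randomised out of the target of 30: 24/30 = 80.0% is go, 23/30 = 76.7% and 22/30 = 73.3% have no verdict, 21/30 = 70.0% and 20/30 = 66.7% are caution, and 19/30 = 63.3% is stop.

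**Step 2: the rows side by side, if both are consented ÷ eligible and the screening go cut-off is 60%.** The last column takes 30 people consenting and solves 30 ÷ E for the number eligible, E.

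| Consented ÷ eligible | Screening row | Recruitment row | E when 30 consent |
|---|---|---|---|
| ≥80% | go | go | 30–37 |
| >70% to <80% | go | none | 38–42 (78.9% to 71.4%) |
| >65% to 70% | go | caution | 43–46 (69.8% to 65.2%) |
| exactly 65% | go | caution and stop | not attainable |
| 60% to <65% | go | stop | 47–50 (63.8% to 60.0%) |
| 50% to <60% | none | stop | 51–60 (58.8% to 50.0%) |
| <50% | stop | stop | 61 or more |

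On this reading the rows give the same verdict only below 50% and at 80% or above. From 60% to <65% they directly contradict each other.

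**Step 3: the other reading of the screening range.** If it means at least 80%, the contradiction at 60% to <65% disappears. The screening row's silent zone then widens from 50% to <60% to 50% to <80%. With 30 consenting, that is 38 to 60 eligible people (78.9% to 50.0%).

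**Step 4: domains promised against rows present.** Section 2.9.5 names four domains: recruitment, retention, adherence and overall acceptability. The table's rows are screening, recruitment, retention and adherence. The number of acceptability rows is zero.

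**The case against.** The strongest objection is that the two rows may not measure the same thing. The recruitment row could mean the share recruited or randomised among people already found eligible and consented. The participant flow leaves room for that: Section 2.5 places a short screening assessment after consent, Table 3 lists consent and baseline measures before randomisation, and Section 3.1 lists screening and recruitment separately. On that reading the go/stop contradiction falls away. It also needs the screening range to mean at least 60%. This stands as a reason to state the contradiction conditionally. It does not rescue the table, because the protocol defines no such separate denominator and the gaps within each row remain.

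The overlap at 65% is a single boundary point, and with exactly 30 consenting the consent proportion cannot equal 65%. That is fair. It is a minor defect, but the boundary still has to be assigned to one band.

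A reader might infer two further things that the document does not support.

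- **That a recruitment-speed criterion is required and missing.** Section 2.9.1 does mention "the possibility of recruiting sufficient participants within a specific period", but among several feasibility measures. Section 3.1 already reports the time to recruit descriptively, no recruitment window is stated, and Section 2.9.5 promises a criterion on recruitment, not on its speed. Adding one is optional.
- **That the rule would force progression despite poor acceptability.** Section 2.9.5 says the criteria help the decision, and acceptability findings feed into it. Nothing says that passing Table 4 compels a full trial. The defect is the narrower one: a criterion is said to be in the table and is not there.

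**Conclusion.** The point holds and should be corrected before results are seen.

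Under any reading, Table 4 is an incomplete rule. The screening row is silent over at least 10 percentage points (50% to <60%), the recruitment row is silent between 70% and 80%, exactly 65% has two verdicts, and the acceptability criterion named in Section 2.9.5 is absent.

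The conflict between the rows is conditional. It assumes that both rows are consented over eligible, which is what the wording suggests, and that the screening go cut-off is 60%. Under those two assumptions, 60% to <65% is go against stop, and >65% to 70% is go against caution. A reader might infer that every consent rate from 50% to just below 80% is established as conflicting or undecided. The document does not support that as a fact, because it leaves the recruitment denominator undefined.

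**What to change.** Rewrite Table 4 before results are seen.

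1. **Define one numerator and one denominator for each row.** Either merge the screening and recruitment rows into a single consent row with one set of cut-offs chosen by the sponsor, or define the recruitment rate as a different quantity, such as randomised out of consented or randomised out of the target of 30.
2. **Use contiguous, non-overlapping bands and replace the range in the screening row with a single go cut-off.** An example built from the recruitment row's cut-offs is go at ≥80%, caution from 65% to <80%, and stop below 65%. If the screening row's lower set is the intended one, its equivalent is go at ≥60%, caution from 50% to <60%, and stop below 50%.
3. **Add an acceptability row** with go, caution and stop bands set in advance on the 14-item satisfaction questionnaire already planned.

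The cost is one revised table and no new data. The downside is that the sponsor must commit to one of its own sets of cut-offs and to an acceptability benchmark that the protocol does not yet contain.
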